### Participant selection

The sample size required for this cohort study is 225 mother-infant pairs, considering the effect size of 0.427 (59), confidence level of 95%, power of 80% and attrition rate of 29.0% (45). First, the list of private hospitals in Selangor will be obtained from the Ministry of Health. Next, eight private hospitals will be randomly selected using a computerized random number generator with an estimated participation of 30 eligible pregnant women per hospital in a month. Pregnant women aged between 18 and 45 years old in their first trimester of pregnancy who visit the selected private hospitals and plan to attend post-natal check-ups for at least 1 year in the study area will be recruited. Meanwhile, pregnant women diagnosed with immune deficiency, severe allergic conditions, psychiatric disorders, multiple pregnancies, preterm delivery (<37 weeks), a newborn with congenital abnormalities, and hospitalized in neonatal intensive care unit immediately after birth will be excluded from this study.

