### Statistical analysis

The IBM SPSS Statistics software version 27 (IBM Corp., Armonk, NY, USA) will be used to analyze the data. Categorical variables will be presented in frequency and percentage, while continuous variables are presented as mean ± standard deviation (SD). The normality of continuous data will be tested using the skewness test (89). Gut microbiota will be analyzed in terms of alpha diversity, beta diversity, and differential abundance of OTUs (87). The incidence rates of asthma, eczema and gastrointestinal disorders among infants will also be calculated. Principal coordinate analysis (PCoA) plots with phylogenetic and non-phylogenetic distances will be plotted (87). One-way ANOVA with corrections (Bonferroni method) and Tukey HSD test will be carried out (89) to test for statistically significant differences in taxonomic richness, diversity measures, bacterial load, and bacterial abundances. Permutational multivariate analysis of variance (PERMANOVA) based on Bray–Curtis distances and 1,000 permutations (89) will be used to evaluate which factors are associated with the composition of the microbiota.

A generalized linear model (GLM) will be used (90) to determine the associations between predictors and gut microbiota and the association between gut microbiota and infant health after controlling for confounders. The strength and precision of each association will be determined using the relative risk (RR) with 95% confidence intervals (CI) after adjusting for potential confounders. The significance level for all statistical analyses will be set at *p* < 0.05. Meanwhile, the Bonferroni correction will be applied to counteract the effect of multiple testing and avoid multiple spurious positives (91). The alpha value will be adjusted to account for the number of comparisons performed (91).

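### Mothers are sampled through eight randomly drawn hospitals, but the sample size assumes independent observations and no named analysis accounts for hospital, so intervals may be too narrow and hospital may confound factors that differ between hospitals

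*Protocol article*

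**What the plan says.** Under Participant selection, the protocol article makes hospital a sampling unit: "eight private hospitals will be randomly selected using a computerized random number generator with an estimated participation of 30 eligible pregnant women per hospital". The sentence goes on to say that this is per month, so 30 is a recruitment rate and not the cluster size. Eligible women attending those hospitals are then enrolled.

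The same section gives the target: "The sample size required for this cohort study is 225 mother-infant pairs". Its inputs are an effect size of 0.427, 95% confidence, 80% power and 29.0% attrition. No ICC or design effect is among them.

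Statistical analysis names three inferential tools:

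- One-way ANOVA with Bonferroni correction and Tukey HSD, for richness, diversity, bacterial load and abundances.
- PERMANOVA on Bray–Curtis "distances and 1,000 permutations (89) will be used to evaluate which factors are associated with the composition of the microbiota". No restriction on the permutations is given.
- "A generalized linear model (GLM) will be used (90) to determine the associations between predictors and gut microbiota", and likewise between microbiota and infant health. It is adjusted for potential confounders that are not listed, with relative risks and 95% intervals.

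Hospital does not appear in that section. No mixed model, GEE, cluster-robust variance or restricted permutation is named.

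**The concern.** Women attending the same hospital may resemble each other in patient mix, obstetric practice and other respects. If that resemblance extends both to an exposure and to the outcome, two things follow. An analysis that treats all mothers as a simple random sample understates the standard error for that exposure. And a difference between hospitals can be read as an effect of the exposure.

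The third specific objective relates socio-demographic, pre-natal and post-natal factors to infant gut microbiota. The Introduction lists delivery mode, maternal medication and the diets of different ethnic groups among the factors of interest. Some of these could plausibly differ from one private hospital to another. Permuting freely across hospitals treats infants from different hospitals as exchangeable, and the sampling scheme gives no ground for that.

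**Working it through.** **1. Reproducing 225.** Inputs from Participant selection: effect size 0.427, read as a standardised mean difference between two equal groups (the article does not say which kind it is); alpha 0.05, taken as two-sided; power 80%; attrition 29%.

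- Per group: 2 × (1.960 + 0.842)² / 0.427² = 2 × 7.849 / 0.1823 = 86.1, rounded up to 87. Total: 174.
- 174 × 1.29 = 224.5, rounded up to 225. This matches the stated target.

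The match uses independent observations, that is, a design effect of 1. Dividing by the retention rate instead gives 174 / 0.71 = 246, so that route leaves no hidden room for clustering within 225 either. (How attrition is applied is a separate matter.)

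**2. Cluster size.** 225 / 8 = 28.1 enrolled per hospital. After attrition 225 × 0.71 = 159.75, and 159.75 / 8 = 19.97, so m is about 20 completers. Equal recruitment across hospitals is an assumption.

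**3. Effect on a test that ignores hospital.** The documents give no ICC, so ranges are assumed. With ρy the outcome ICC and ρx the exposure ICC:

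- design effect DE = 1 + (m − 1) × ρy × ρx
- standard error understated by a factor √DE
- actual level of a nominal 5% two-sided test = 2 × [1 − Φ(1.96 / √DE)]

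Example: ρy = 0.05, ρx = 1 gives DE = 1 + 18.97 × 0.05 = 1.948 and √DE = 1.396. Then 1.96 / 1.396 = 1.404, and the level is 0.160.

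| Exposure | ρy = 0.01 | ρy = 0.02 | ρy = 0.05 |
|---|---|---|---|
| Constant within hospital (ρx = 1) | DE 1.19, level 7.2% | DE 1.38, level 9.5% | DE 1.95, level 16.0% |
| Partly clustered (ρx = 0.3) | DE 1.06, level 5.7% | DE 1.11, level 6.3% | DE 1.29, level 8.4% |
| Mostly individual (ρx = 0.1) | DE 1.02, level 5.2% | DE 1.04, level 5.4% | DE 1.10, level 6.1% |
| No clustering of exposure (ρx = 0) | DE 1.00, level 5.0% | DE 1.00, level 5.0% | DE 1.00, level 5.0% |

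The top row is the upper limit for each outcome ICC. There the standard error is understated by factors of 1.09, 1.17 and 1.40.

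**4. Can the named methods carry hospital?** One-way ANOVA has a single factor, so it cannot. PERMANOVA can, through restricted permutation, but the article specifies the distance and the number of permutations and stops there. The GLM can, if hospital is among its unlisted confounders.

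**The case against.** The strongest reply is that a journal article condenses the full plan, and that covariate lists, variance estimators and permutation strata are commonly left to that plan. For the GLM this stands. A reader might infer that the GLM omits hospital, but the article lists no confounders at all, so hospital is no more excluded than any other covariate. The reply does not cover one-way ANOVA, which cannot take a hospital term however the full plan reads, or the sample size, which is stated as final and reproduces without any clustering.

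A second reply is that the upper-limit figures fit no exposure the study names. This is largely right. The factors in the objectives are measured on individual mothers and infants, and for most of them the lower rows of the table are the relevant ones. A flat statement that the confidence intervals are too narrow would not be supported.

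Third, a reader might infer that hospital differences do confound the associations. The documents do not show this. The article does not say that women deliver at the hospital that recruited them, and all sites are private hospitals in one state, which may limit differences between them. Nor is there much support for hospital-specific sample handling as a route: mothers collect samples themselves with supplied kits, and everything goes to one university laboratory and then to one analysis centre, although the Discussion concedes handling differences as a possible limitation. Confounding by hospital remains a risk, not an established fact.

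**Conclusion.** The point holds in conditional form. Hospital is a sampling stage by design, 225 makes no allowance for it, and the tests as named do not account for it. For a factor that clusters by hospital, intervals may be too narrow and hospital may confound the association.

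The inflation ranges from none, through 5.2% to 6.1% for a mostly individual-level factor, to 7.2% to 16.0% at the limit of a factor constant within hospital. These figures rest on outcome ICCs of 0.01 to 0.05, the exposure ICCs shown and equal recruitment, all of them assumed. The documents establish neither that the GLM leaves hospital out nor that confounding is present. The change should still be made: hospital is known at enrolment, the remedy is cheap, and ignoring the sampling units would be hard to defend later.

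**What to change.** - **Association models:** include hospital as an eight-level fixed effect. With only eight clusters this is preferable to uncorrected cluster-robust standard errors. Use a random intercept where the outcome is too rare for seven extra terms. Using the prevalences in the Introduction as a guide, 160 completers would give about 44 infants with eczema (160 × 0.276) but only about 10 with wheezing (160 × 0.061). The random intercept deals with the correlation but removes between-hospital confounding less completely.
- **Group comparisons:** replace one-way ANOVA by a linear model with group and hospital. Bonferroni and Tukey comparisons can then be made on the adjusted means.
- **PERMANOVA:** restrict permutations to within hospital.
- **Participant selection:** state that 225 makes no allowance for clustering by hospital.

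No new data are needed. The cost is seven degrees of freedom. With the fixed effect, or with permutation within hospital, characteristics constant within a hospital cannot be estimated or tested; the stated objectives name none.

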### Data collection timeline

Data collection will be conducted from June 2022 to December 2024. Once the recruitment of participants begins, pregnant mothers in their first trimester will be given an information sheet explaining the purpose of the study, and those who agree to join the study are required to provide written informed consent. Data will be collected from the eligible pregnant women during their first trimester (8–12 weeks), second trimester (24 weeks), third trimester (34 weeks) and follow-up infants and mothers post-natally after birth (1–5 days after delivery), at 10–15 days, 1 month, 4 months, 6 months and 12 months of age with a total of nine follow-ups to collect mother-infant biological samples and other relevant information for the research. Types of data and samples to be collected from mothers and infants at each time point are summarized in Figure 1.

**Figure 1 F1:**
[figure not shown]
Data collection time points and sample collections of mothers and infants.

### Measurements

#### Anthropometric assessments

Maternal pre-and post-pregnancy body weight, current weight, and height will be extracted from the medical records to determine pre-and post-pregnancy BMI and gestational weight gain. Meanwhile, the infant's birth weight, current weight, length and head circumference at birth will be obtained from the child health record book. In addition, infants will be measured by researchers for their mid-upper arm circumference (MUAC), triceps skinfold (TSF) and subscapular skinfold (SSF) at 1, 4, 6, and 12 months by using a Lufkin Executive Diameter steel tape model W606PM (Cooper Hand Tools, Raleigh, North Carolina, USA) and Harpenden skinfold caliper (British Indicators Limited), respectively.

#### Biochemical assessments

A venous blood sample (6 ml) will be collected from the pregnant mothers during their routine antenatal check-ups in their first, second, and third trimester and 12 months after delivery by a certified phlebotomist. The blood will be analyzed for serum 25(OH) D level (45), iron, lipid, and metabolome profiles (60, 61) of the mothers. About 100 mg of blood sample will be mixed with 0.6 mL of 2-chlorophenylalanine-methanol solution in a 2 mL EP tube for vortex of 30 s, and then will be grinded, treated with ultrasonic, and centrifuged. Supernatant samples will be filtrated and detected with LC-MS (60). Breast milk samples are self-collected by mothers (62) at 1–5 days, 10–15 days, 1 month, 4 months, and 12 months after delivery. Human milk glycerides, phospholipids, and sphingolipids will be profiled using ultra-performance liquid chromatography/quadrupole-time-of-flight mass spectrometry [UPLC/Q-TOF-MS with electrospray ionization source (ESI)] (63). Meanwhile, the human milk oligosaccharides (HMO) will be quantified using ultra-high-pressure liquid chromatography (UHPLC) with fluorescence detection (64). Next, the membrane protein of milk fat globules will be analyzed with the high-pressure liquid chromatography Q-Exactive mass spectrometry (HPLC-QE MS) (65). Next, the immune parameters and cytokine profiles from human milk will be determined using the Luminex-approach and ELISA kits. Finally, the fatty acids composition analysis will be conducted using transmethylation techniques, capillary gas chromatography, and flame ionization (66).

#### Clinical data

Pregnant mothers will be interviewed upon recruitment using a pre-tested questionnaire. The information that will be collected includes socio-demographic data (parents' age, ethnicity, educational background, occupation, monthly household income, and marital status), obstetric history (gravida, parity, and smoking during pregnancy), and exposures (antibiotics, prebiotics, probiotics, paracetamol, and family history of diseases, exposure to smoke or second-hand smoke, alcohol consumption, constipation, emotional status, sleep, and disease development). Additionally, their prenatal blood pressure will be retrieved from the medical records.

#### Dietary assessments

Mothers will be interviewed about their dietary intake using a 24-h dietary recall at the first, second, and third trimester, and each visit at 1, 4, 6, and 12 months after birth. The dietary data will be analyzed using NutritionistPro^TM^ software (Axxya Systems, Redmond, Washington, USA) for energy and nutrients based on the Malaysian Food Composition Database (67) and the ASEAN Food Composition Database (68). Energy and nutrient adequacies are determined based on the Recommended Nutrient Intake (RNI) for Malaysians (69). Furthermore, mothers are interviewed for their infant's dietary intake using a 24-h dietary recall at 1, 4, 6, and 12 months. Infant feeding practices will also be assessed at one, four, six, and 12 months (70). The dietary diversity score will be calculated based on the infant and young child feeding (IYCF) criteria, which includes the intake of seven food groups (grains, roots and tubers, legumes and nuts, dairy products, flesh foods, eggs, vitamin A-rich fruits and vegetables, and other fruits and vegetables) (71).

#### Questionnaires

A set of validated questionnaires will be used to collect information at different time points as the following:

Physical activity: Pregnancy Physical Activity Questionnaire (PPAQ) (72);Food security: Six-item U.S Department of Agriculture (USDA) Food Security Survey Module (FSSM) (73);Stress during pregnancy: Perceived Stress Scale (PSS)-10 (74);Depression: Edinburgh Postnatal Depression Scale (EPDS) (75);Gastrointestinal disorders of infants: Rome IV Diagnostic Questionnaire for Pediatric Functional Gastrointestinal Disorders-Toddler (R4PDQ-Toddler) (76);Infant temperament: Revised Infant Behavior Questionnaire (IBQ-R) (77);Presence of eczema in infants: five questions of the UK Working Party's Diagnostic Criteria for Atopic Dermatitis (78);Severity of eczema symptoms in infants: Patient-Oriented Eczema Measure (POEM) for children (79);Asthma symptoms in infants: Asthma Predictive Index (API) (80);Appetite traits: Baby Eating Behavior Questionnaire (BEBQ) (0–5 days, 10–15 days and 1 month) (81) and Children Eating Behavior Questionnaire (CEBQ) (4, 6, and 12 months) (82);Developmental delays: Ages and Stages Questionnaire, third edition (ASQ-3) (83).

#### Microbiota

##### Collection and transportation of samples

Saliva, urine, and feces self-collection kits will be given to mothers at each visit. Saliva sample will be collected using an oral salivary swab. Mothers are required to remove the swab from Salivette^®^ (Sarstedt, Nümbrecht, Germany) tube and gently roll her and her infant's mouth for 60 s before placing the swab into the salivette tube, per the manufacturer's instructions (65). Urine samples will be collected for metabolomic analysis using a urine collection container with boric acid as the preservative. Fresh feces from mothers and infants will be self-collected into a 5 mL feces collection tube (Sarstedt, Nümbrecht, Germany) with 2 mL of ribonucleic acid (RNA) (65). After collection of the feces sample, the cap of the feces tube will then be closed tightly followed by the shaking of tube for several times. A pad is placed in the diaper and used to collect unsoiled urine and fecal samples from the infant (65).

Mothers will be given a reminder *via* text and a tutorial video about the timing and methods of self-collection and storage of samples. They are required to notify the researchers once the self-collection and storage are done for transportation arrangements to the laboratory. All biological samples collected will be stored immediately inside a portable insulated container with ice packs at −20 °C and transported within 24-h of collection to the nutrition laboratory at Universiti Putra Malaysia for storage at −80 °C until further analysis. Once all the samples are prepared, aliquots labeled with the specific study ID number without personal information will be air freighted on dry ice and shipped to the National Engineering Center of Dairy for Maternal and Child Health, Beijing, China for further analysis.

##### Microbiome analysis

The saliva, urine, and fecal samples collected will be analyzed to examine microbiota diversity, richness, and taxonomic composition (65). First, the genomic DNA will be extracted from homogenized fecal samples using the QIAamp Fast DNA Stool Mini Kit (Qiagen, GmbH, Hilden, Germany), following the manufacturer's instruction (65). Then, the polymerase chain reaction (PCR) amplification of the V3-V4 region of 16S rRNA genes with primers Bakt_341F(CCTACGGGNGGCWGCAG) and Bakt_805R (GACTACHVGGGTATCTAATCC) (84) will be performed as the following protocol: 3 min at 95 °C, 25 cycles of 30 s at 95 °C, 30 s at 55 °C, and 30 s at 72 °C (65). Taq DNA polymerase used is the Phusion^®^ High-Fidelity DNA polymerase (M0530S, New England Biolabs, USA). Sequencing libraries will be generated using NEBNext^®^ Ultra DNA Library Prep Kit for Illumina (New England Biolabs, USA). Amplicons will be sequenced using 2 × 250 base pair (bp) paired-end protocol by Illumina HiSeq 2500. USEARCH (version 1.9) (85) will be used to quality filter, cluster, and remove chimeras from demultiplexed 16S rRNA raw sequencing data of the samples. The clustered sequences at 97% similarity level will be utilized to construct operational taxonomic units (OTU) tables and representative sequences will be assigned taxonomy from phylum to species based on the Ribosomal Database Project (RDP) 16S rRNA training set (Version 16) (86).

##### Metabolome analysis

The composition of short-chain fatty acids (SCFAs) will be identified by using the high pressure liquid chromatographic methods (Jasco Corporation, Japan) (87) and nuclear magnetic resonance (NMR) spectroscopy (88). First, the sample will be homogenized and centrifuged at low speed, and the supernatants will be filtered and mixed with phosphoric acid 0.1% as a mobile phase. Then, the mixture will be injected into the HPLC system, comprising a column Rezex™ ROA-Organic Acid H+ (8%), LC Column 300 × 7.8 mm, (Phenomenex, USA) and a UV detector at 210 nm (87). Next, the immune parameters and cytokine profiles from feces and saliva will be analyzed using the Luminex-approach and ELISA kits (87). Concentrations of the specific cytokines and the chemokines, macrophage migration inhibitory factor, macrophage inflammatory protein-1-α, monocyte chemo-attractant protein-1, immunoglobulins, and eotaxin will be determined (87). Both feces and urine samples will be further analyzed for metabolome using the NMR spectroscopy analysis (65, 88). The samples will be centrifuged, and an aqueous layer will be transferred into a 2 mL centrifuge tube. Finally, the samples will be mixed with 3-(trimethylsilyl)-1-propanesulphonic acid sodium salt (DSS) standard solution before being transferred into a tube for NMR spectroscopy analysis (65).

### Statistical analysis

The IBM SPSS Statistics software version 27 (IBM Corp., Armonk, NY, USA) will be used to analyze the data. Categorical variables will be presented in frequency and percentage, while continuous variables are presented as mean ± standard deviation (SD). The normality of continuous data will be tested using the skewness test (89). Gut microbiota will be analyzed in terms of alpha diversity, beta diversity, and differential abundance of OTUs (87). The incidence rates of asthma, eczema and gastrointestinal disorders among infants will also be calculated. Principal coordinate analysis (PCoA) plots with phylogenetic and non-phylogenetic distances will be plotted (87). One-way ANOVA with corrections (Bonferroni method) and Tukey HSD test will be carried out (89) to test for statistically significant differences in taxonomic richness, diversity measures, bacterial load, and bacterial abundances. Permutational multivariate analysis of variance (PERMANOVA) based on Bray–Curtis distances and 1,000 permutations (89) will be used to evaluate which factors are associated with the composition of the microbiota.

A generalized linear model (GLM) will be used (90) to determine the associations between predictors and gut microbiota and the association between gut microbiota and infant health after controlling for confounders. The strength and precision of each association will be determined using the relative risk (RR) with 95% confidence intervals (CI) after adjusting for potential confounders. The significance level for all statistical analyses will be set at *p* < 0.05. Meanwhile, the Bonferroni correction will be applied to counteract the effect of multiple testing and avoid multiple spurious positives (91). The alpha value will be adjusted to account for the number of comparisons performed (91).

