The rising attention of good gut health development in infants to ensure optimal child development in Malaysia (52–55) necessitates this prospective cohort study. The major contributions of this study would include the prospective cohort study design and providing clarity of temporal sequence between exposures and outcome. This study involves comprehensive and prospective quantitative assessments of mothers and infants. Besides, frequent collections of urine, feces, saliva, and breast milk samples enable a holistic assessment of maternal and infant gut microbiota over time, identifying the microbiota alterations and abundance. However, one of the limitations of this study is the multiple assessments on the pregnant women during their first, second and third trimesters until 12 months postpartum, which could be potentially burdening and lead to high dropout rates. The commitment required in the collection and delivery of bio-samples in the morning may be burdensome for working mothers. These situations will be addressed by providing incentives per visit and a summary of findings and reminders about all the follow-up activities *via* phone calls and text messages. Another possible limitation is the compliance of mothers and infant sample collections (saliva, feces, urine, and breastmilk). This limitation will be overcome using user-friendly self-collection kits with clear instructions and reminders by the researchers. Furthermore, the researchers will collect samples, thus easing the burden of respondents. Besides, there are concerns on the response and social desirability bias due to the self-report nature of the questionnaire on infant health, including temperament, gastrointestinal disorders, eczema, asthma, and developmental delays. Moreover, differences in sample handling protocols, collection procedures and processing data pipelines could be the limitation of this study.

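### The only test named for differences in richness, diversity, load and abundance is one-way ANOVA, which does not fit comparisons across visits of the same infants

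*Protocol article*

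**What the plan says.** **Design.** After birth, infants are seen at 1–5 days and then "at 10–15 days, 1 month, 4 months, 6 months and 12 months of age" (Data collection timeline). That makes six post-natal time points. Under Collection and transportation of samples, feces kits are handed out at every visit and infant feces are collected. Up to six stool samples per infant is therefore an inference; Figure 1, which sets out samples by visit, is not available here.

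**Aim.** The Introduction notes that earlier local cohorts did not follow infant microbiota over time, and objective 1 is to assess it through the first year. The Discussion names as a strength that "frequent collections of urine, feces, saliva, and breast milk samples enable a holistic assessment of maternal and infant gut microbiota over time". Objectives 3 and 4, on associations with the microbiota and with infant health, are set at 12 months.

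**Analysis.** For richness, diversity measures, bacterial load and bacterial abundances: "One-way ANOVA with corrections (Bonferroni method) and Tukey HSD test will be carried out (89) to test for statistically significant differences in taxonomic richness". PERMANOVA with 1,000 permutations on Bray–Curtis distances is named for factors associated with composition, and a generalized linear model (GLM) for the two sets of associations. The section gives no ANOVA grouping factor, no visit for any test and no permutation scheme. It names no mixed model, repeated-measures ANOVA or GEE.

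**The concern.** One-way ANOVA with Tukey HSD assumes that the groups being compared are independent. Visits of the same infants are not. When visits are the groups, stable differences between infants stay in the error term although they cancel from every visit-to-visit contrast. The test becomes conservative and loses power for change over the first year, which is the reason for running this cohort.

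This goes beyond detail that a condensed article may leave out: a specific test is named, and it does not fit the repeated samples. An analysis plan that followed the article would carry the misfit forward.

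**Working it through.** **Inputs from the article.** "The sample size required for this cohort study is 225 mother-infant pairs", with effect size 0.427, 95% confidence, 80% power and 29.0% attrition (Participant selection); a 0.05 significance level (Statistical analysis); six post-natal time points.

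**Assumed, not in the article.** Two-sided testing; 0.427 read as a standardised mean difference; within-infant correlation ρ of 0.1, 0.3 or 0.5, equal between all pairs of visits; equal variance at each visit; complete data; a 0.25 SD change as the illustration.

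**1. The plan's own figure.** Per group: 2 × ((1.960 + 0.842)/0.427)² = 86.1, rounded up to 87, so 174 in total. Then 174 × 1.29 = 224.5, rounded up to 225, which matches. The number left after 29% attrition is 225 × 0.71 = 159.75, so 160 infants are used below. (Whether attrition should be applied by multiplying is a separate matter.)

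**2. Two visits compared, n = 160, change 0.25 SD.**
- Standard error used by the unpaired test: √(2/160) = 0.1118, so the difference must exceed 1.96 × 0.1118 = 0.2191.
- True standard error: √(2(1 − ρ)/160), which is 0.0935 at ρ = 0.3.
- Unpaired power at ρ = 0.3: Φ((0.25 − 0.2191)/0.0935) = Φ(0.330) = 63%.
- Paired power at ρ = 0.3: Φ(0.25/0.0935 − 1.96) = Φ(0.713) = 76%.

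| ρ | Unpaired power | Paired power |
|---|---|---|
| 0.1 | 61% | 65% |
| 0.3 | 63% | 76% |
| 0.5 | 65% | 89% |

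These are for a single contrast at 5%, before any Bonferroni or Tukey adjustment.

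**3. All six visits compared.** Simulation with 160 infants and 3,000 runs per correlation. The drift is linear, reaching 0.25 SD from first to last visit.

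| ρ | True size of one-way ANOVA (nominal 5%) | Power, one-way ANOVA | Power, repeated-measures ANOVA |
|---|---|---|---|
| 0.1 | 3.2% | 49% | 57% |
| 0.3 | 0.8% | 40% | 67% |
| 0.5 | 0.03% | 32% | 84% |

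**4. One visit only, two infant groups.** In the same simulation, one-way ANOVA on a single sample per infant had size 5.8%, 4.3% and 5.0% at the three correlations. There is no problem here.

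**5. Conditional case: infant groups compared with all six visits pooled.** The article does not say that this will be done. The design effect is 1 + 5ρ = 1.5, 2.5, 3.5. The true size is 2(1 − Φ(1.96/√(design effect))) = 11%, 22%, 29%; simulations gave 11–12%, 20–22% and 29–30%. Confidence intervals would have 1/√(design effect) = 82%, 63%, 53% of the correct width. For PERMANOVA on pooled samples (simulated with 40 infants, 15 taxa, 199 permutations, 200 runs), free permutation gave 12.5% and 50.5% at ρ = 0.1 and 0.3. Permuting whole infants gave 3.5% and 6%.

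**The case against.** The strongest reply is that the article never says visits will be pooled, or even that ANOVA will compare visits. Objectives 3 and 4 are fixed at 12 months. The GLM serves exactly those two, and PERMANOVA most naturally serves objective 3. With one sample per infant there is no within-infant correlation, and step 4 confirms that the tests then keep their level. All of this stands.

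A reader might infer that all three methods treat correlated samples as independent and that group effects will be declared significant at something like 22% instead of 5%. The article does not support that. It gives neither a permutation scheme nor a GLM covariance structure, and such detail may sit in a fuller document.

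It can also be said that objective 1 is worded descriptively, that one-way ANOVA across visits errs on the safe side, and that a 0.25 SD change may be small beside the large transitions the Introduction describes. The direction of error is as stated: no excess of false positives arises from comparing visits. For large changes the lost power would matter less; for subtler ones it would matter.

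What the reply does not remove is that microbiota over time is a stated purpose and that the only test of differences named for richness, diversity, load and abundance is one for independent groups.

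**Conclusion.** The point holds for comparisons across visits and for any analysis that combines visits, and no further. For comparisons across visits, one-way ANOVA is conservative: at assumed correlations of 0.1 to 0.5 its true size over six visits runs from about 3% to below 0.1%. At correlation 0.3, power for a 0.25 SD change between two visits is about 63% instead of 76%. Any positive correlation gives an error in this direction; its size rests on the assumed correlation, 160 completers, up to six samples per infant and the chosen change.

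The inflation of type I error to about 11–30% is conditional on pooling visits to compare infant groups, which is not in the plan, and should not be cited as a property of it. The 12-month analyses are not called into question. This should be fixed and is cheap to fix.

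**What to change.** In the Statistical analysis section:

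- State the visit, or visits, and the grouping factor for each test.
- For comparisons across visits of richness, diversity, bacterial load and abundance, replace one-way ANOVA with a linear mixed model with an infant random intercept and visit as a fixed effect. SPSS MIXED, within the package already named, fits this.
- Where an association analysis combines visits, use GEE or a mixed model in place of a GLM for independent observations.
- Where PERMANOVA combines visits, permute within infant for visit effects and by whole infant for infant-level factors.
- Keep one-way ANOVA, PERMANOVA and the GLM as written for single-visit analyses, including objectives 3 and 4.

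The cost is a few sentences of wording and slightly more analysis work. No new data, visits or participants are needed.
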